### Research Questions

1. Do youth (12 to 17 years of age) who engage in the 6-month HELP e-intervention have a larger improvement in emotional health (measured by the Strengths and Difficulties Questionnaire) than youth who do not receive the intervention?
2. Does engagement in the HELP e-intervention improve lifestyle behaviour (physical activity, sleep or screen time)?
3. Are changes in emotional health and lifestyle behaviours sustained for at least 6 months after completion of the HELP e-intervention?
4. Do youth who engage in the 6-month HELP e-intervention utilize fewer mental healthcare resources, during and for 1 year following RCT participation, than youth who do not receive the intervention?
5. Do mental health professionals supporting youth who engage in the 6-month HELP e-intervention provide lifestyle behaviour support less frequently than for youth who do not receive the intervention?
6. Are self-reported (i.e., perceived) lifestyle behaviour changes (study questionnaire responses) aligned with objective measures of screen time (smartphone tracking) and sleep and physical activity (accelerometry) in a randomly selected sub-sample (1 of 3) enrolled participants?

We hypothesize that youth engaging in the HELP e-intervention will have improved emotional health and enhanced lifestyle behaviours in comparison to those receiving the delayed (post 6-months) intervention. We hypothesize that changes during the intervention will be maintained for an additional 6 months, and that self-reported measures will accurately reflect objective measurements. We hypothesize that youth engaging in the HELP e-intervention will require fewer youth mental health supports, and when supported will be less likely to require treatment directed at lifestyle behaviours.

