# Study Design

This research will investigate the patient and healthcare system impacts of the HEalthy Lifestyle Project (HELP) e-intervention. The research design is a randomized, controlled trial comparing youth who immediately receive the intervention to youth randomized to receive the intervention 6-months later (wait list control). Efficacy outcomes will be assessed at 0, 3, 6 and 12 months. Healthcare system impacts will be extracted from medical records from 0 to 18 months.

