## Study Procedures/Evaluations

### Recruitment

The primary avenue for recruitment will be via 1Call1Click. During our pilot study of the HELP e-intervention (REB #21 85X) we developed a best practice advisory flag within EPIC (Appendix A) that was provided to 1Call1Click intake staff if the youth met the age criteria for the research study. Youth who access 1Call1Click have an initial assessment by intake staff. Staff have information about the research study and have been educated regarding the inclusion/exclusion criteria. If the research study could be appropriate for the patient, the intake staff will ask the patient/family if they would like more information about research. If the response is positive, intake staff will send an EPIC inbasket message to the research team who will follow up with the patient/family to discuss the study details.

During the pilot study we also received feedback from youth, families and clinicians requesting that the HELP e-intervention be more widely available to youth who are at various stages in their journey to mental wellness. Therefore, additional youth may be recruited through our two secondary recruitment options. CHEO mental health clinicians will be able to refer youth for enrollment in the research study if they have obtained permission from the youth to do so. This avenue for recruitment will enable youth on the wait list for specialist support or who are currently receiving CHEO support to be eligible for study recruitment. We will also distribute the study information via posters (Appendix B) and social media posts (Appendix C) in CHEO patient areas and through our youth partner groups (CHEO Youth Forum, CHEO-RI Family Leader Program, YouthNet / R$é$seau Ado, the study’s Lived Experience Advisory Group, etc.). Youth who contact the research team after viewing the study information will also be eligible to enroll.

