### Study Assessments

A researcher blinded to study group allocation will work with enrolled youth to complete all study assessments. The accurate/reliable study questionnaires include measures of emotional strength (Strengths and Difficulties Questionnaire)^34^, lifestyle choices (Youth Quality of Life-short form)^35^, readiness for behaviour change (Stages of Change Questionnaire^36^), and sleep (Adolescent Sleep Hygiene Scale)^37^, physical activity (Habitual Activity Estimation Scale)^38^, and leisure screen time (Adolescent Sedentary Activity Questionnaire)^39^ behaviours. All enrolled youth will complete all questionnaires at 0, 3, 6 and 12 months. As in our pilot study (REB #21 85X), the questionnaires (Appendix E) will be completed virtually using RedCAP, with automated scoring of the responses according to published methods. At each assessment, youth will be asked to voluntarily self-report age (years), gender (boy, girl, unkown, other, prefer not to answer), and their use of other mental health therapies (Appendix F). Study enrollment does not restrict access to or use of other mental health supports.

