The research coordinator will collect the healthcare system impact outcomes via medical chart review after participants have completed the 12-month assessment. For the 18 months after study enrollment, we will record the number and type of youth mental healthcare system contacts (request for support, appointment scheduling, treatment visit). We will also track the number, type (e.g., community provider, peer support, outpatient, day treatment, inpatient), purpose (assessment, counselling), professional seen (e.g., psychiatrist, psychologist, social worker, nurse) and length (visit length in minutes) information for each service delivery visit (i.e., appointments/visits with any type of mental healthcare service provider). Health record notes for all mental healthcare visits will be reviewed in detail to identify all content related to sleep, physical activity or screen time assessments, discussions or recommendations for change. The complete text of each lifestyle-related clinic note will be de-identified for any patient-specific information before being transferred to our research database. Sex and mental health diagnoses will also be extracted from health records.

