### Healthcare System Outcomes

Measures of youth mental healthcare system utilization will be compared between the intervention and wait list control participants. Independent t-tests will compare the number of system contacts, number of service delivery visits and length of service delivery visits for each timeframe (with/without intervention access). Chi-square statistics will compare categorical variables (type of system contacts, type of service delivery visit, professional seen, purpose of service delivery visit) between the intervention and control participants for each timeframe. Linear regression models will compare these outcomes between the intervention and control participants, adjusting for demographic variables (age, sex, mental health concern). Repeated measures models will evaluate the pattern of changes to mental health service use throughout study participation.

The frequency of lifestyle support during mental health services will be evaluated using mixed methods. Each comment in the research database will be coded to indicate the focus (assessment, discussion, recommendation), content and information conveyed by the comment utilizing the same procedures and coding framework developed during our retrospective chart review^44^. Descriptive statistics (frequency tabulations, means or medians (variance) as appropriate) are then used to summarize the data. We will also analyze these data qualitatively, using an inductive approach (no preconceived coding framework). Independent analyses of the qualitative data will be completed by two members of the research team to summarize the lifestyle-related discussions during patient visits. Inductive analyses will begin with data immersion, reading/re-reading the extracted comments. Analytical notes and key phrase identification will identify concepts and enable initial code creation (NVivo nodes). Analyses, interpretation and revisions will continue throughout the analytical process. Data will be interpreted relative to understanding lifestyle needs and counselling for these youth. Key findings will be reviewed separately by age group (12-14, 15-17), sex and type of treatment to identify any trends suggesting that lifestyle needs vary systematically.

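### Chart-derived service outcomes (research questions 4 and 5) have no pre-enrolment window, so the service-use comparison forgoes a prior-use covariate and the precision it could add

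*Protocol*

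**What the plan says.** The extraction window is stated consistently. Study Design has "Healthcare system impacts will be extracted from medical records from 0 to 18 months", Study Assessments has "For the 18 months after study enrollment, we will record the number and type of youth mental healthcare system contacts", and the note under the schedule table in Expected Duration of Participation also counts 18 months from enrolment.

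Research question 4 asks whether HELP youth "utilize fewer mental healthcare resources, during and for 1 year following RCT participation, than youth who do not receive the intervention". Research question 5, on lifestyle support given by mental health professionals, draws on visit notes from the same chart review.

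Under Healthcare System Outcomes, "Independent t-tests will compare the number of system contacts, number of service delivery visits and length of service delivery visits for each timeframe". Linear regressions follow, "adjusting for demographic variables (age, sex, mental health concern"), and no prior-use term is listed. Finally, "Repeated measures models will evaluate the pattern of changes to mental health service use throughout study participation"; that period begins at enrolment.

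Other outcomes do have a starting value: "All enrolled youth will complete all questionnaires at 0, 3, 6 and 12 months", and the accelerometer and screen-use measures are taken at months 0 and 6. Recruitment is open beyond first contacts, including "youth on the wait list for specialist support or who are currently receiving CHEO support".

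**The concern.** A participant already in regular treatment and one making a first call are likely to differ in later service use whichever arm they join. With no count from before randomisation, whatever part of that difference earlier use could explain stays in the error term of the t-tests and regressions. A chance difference between arms in prior use could be neither seen in the chart data nor adjusted for.

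This is a protocol matter and not only one for the analysis plan. An analysis plan can choose covariates, but it cannot adjust for a period that the protocol does not extract. At stake is how sharply research question 4 can be answered. Research question 5 has the same gap, with less consequence, because its analysis is described as descriptive and qualitative.

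**Working it through.** **Inputs from the protocol.** Complete data on 122 youth, 80% power and a 3.4-point difference on the Strengths and Difficulties Questionnaire (Sample Size Determination); significance at 0.05 (Data Analyses). No power statement exists for service use.

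**Assumptions.** Equal allocation (61 per arm), a two-sided test, the normal approximation, an illustrative 0.4 SD difference in service use, and r from 0.2 to 0.7. Because the planned regression already includes age, sex and mental health concern, r is best read as the correlation that remains after those terms.

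**The plan's own figure.** No SD is given, so 122 can only be back-solved.
- Detectable difference in SD units = (1.960 + 0.842) × √(2/61) = 2.802 × 0.181 = 0.507.
- Implied SD = 3.4 / 0.507 = 6.70 points.

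This shows what the figure assumes. It is not an independent check, and it concerns the questionnaire, not service use.

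**Effect of a prior-use covariate.** Adjustment multiplies the residual variance by 1 − r². Then:
- detectable difference = 0.507 × √(1 − r²)
- power = Φ(0.4 / [0.181 × √(1 − r²)] − 1.960)
- unadjusted N of equal precision = 122 / (1 − r²)

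| r | 1 − r² | Detectable difference (SD) | Power for 0.4 SD | Equivalent unadjusted N |
|---|---|---|---|---|
| none | 1.00 | 0.507 | 59.8% | 122 |
| 0.2 | 0.96 | 0.497 | 61.6% | 127 |
| 0.3 | 0.91 | 0.484 | 63.9% | 134 |
| 0.5 | 0.75 | 0.439 | 72.3% | 163 |
| 0.7 | 0.51 | 0.362 | 87.1% | 239 |

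**Over the expected enrolment of about 100 to 200**, if all have complete data, power for 0.4 SD at r = 0.5 rises from 51.6% to 63.7% at N = 100, and from 80.7% to 90.4% at N = 200.

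**Chance imbalance.** The difference between arms in mean prior use has a standard error of √(2/61) = 0.181 SD. It exceeds 0.25 SD in either direction in about 17% of trials (0.25 / 0.181 = 1.38). At r = 0.5 such an imbalance moves the unadjusted service-use difference by 0.5 × 0.25 = 0.125 SD, or 0.125 / 0.181 = 0.69 of its standard error.

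**The case against.** The best defence is that nothing is wrong with the inference. Allocation is random, so arms differ in prior use only by chance, and the unadjusted standard error already includes that chance. The 17% figure describes ordinary sampling variation. This stands: the loss is precision, not validity.

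A reader might infer that the repeated measures models lack any HELP-free reference, because the immediate arm's first period is already on HELP. That is true only within that arm. Research question 4 is a comparison between groups, and the wait-list arm has no HELP access in months 0 to 6, so it supplies the reference.

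A reader might also infer that there is no baseline information at all. There is some. Youth are asked at every assessment, month 0 included, about use of other mental health therapies (Study Assessments), and support referral is a covariate in the efficacy models (Efficacy Outcomes). The self-report is voluntary and not a chart count, and neither item is listed for the service-use models. They narrow the gap but do not close it.

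The gain may also be small. Central intake is the main recruitment route, so many youth may have little recorded earlier use. Youth on a wait list may have low past and high later use. Earlier community or peer-support visits may be missing from the chart. Each would lower r. All of this stands as a limit on the size of the benefit. Covariate choice can wait for an analysis plan; the extraction window cannot.

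**Conclusion.** The point holds as an inexpensive improvement in precision, not as an error or a source of bias. The chart window begins at enrolment, the listed service-use covariates omit prior use, and entry deliberately mixes stages of care.

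On the stated assumptions, power moves from about 60% to about 64% (r = 0.3) or 72% (r = 0.5), and by less than 2 points at r = 0.2. The effect size and r are not in the documents, and 61 per arm is borrowed from the questionnaire calculation, so these figures show a range and not an expected gain.

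Two stronger readings are not supported. Service use is not the only outcome without a baseline, because research question 5 shares the gap. Nor do the documents say how well prior use predicts later use, so it cannot be called the strongest predictor.

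**What to change.** - **Study Design and Study Assessments:** add a fixed look-back before enrolment, for example 6 or 12 months, for counts of contacts and visits by type only. Earlier notes need not be coded, so research question 5 would remain without a baseline.
- **Healthcare System Outcomes:** make the main between-arm comparison of service use the regression that includes the same measure's pre-enrolment count, alongside the covariates already listed.
- **At the least:** add month-0 self-reported therapy use and support referral to the service-use models. This needs no further chart extraction. Support referral is defined by central intake, so it may be missing for youth recruited by other routes.

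**Cost.** The chart review is already retrospective and follows the 12-month assessment, so the look-back adds extraction time per participant but no new data source. Inclusion criterion (f) covers consent to evaluate healthcare outcomes from the record; whether that reaches earlier records is not clear, so consent and research ethics board wording should name the period, preferably before recruitment proceeds. Possible under-recording of earlier community and peer-support visits should be stated as a limitation.

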### Summary of Work to Date

Our review of the medical records for 102 youth receiving specialist mental health support at CHEO found lifestyle counselling was included within mental health treatment for 95% of patients. In response, the expertise of 10 youth inpatients, 10 youth outpatients, 10 parents and 10 clinicians defined their desired type of lifestyle support. The HEalthy Lifestyle Project (HELP) resources were then iteratively and collaboratively designed with 12 inpatients, 33 outpatients, 18 parents, 11 clinicians and 23 Indigenous youth and elders (CHEO REB#20 62X).

Our pilot study of the HELP e-intervention enrolled youth contacting 1Call1Click or on the CHEO waitlist for specialist mental health services (CHEO REB#21 85X). 42% of youth waiting for specialist mental health support were eligible. Student researchers were able to approach 62% of eligible youth and successfully recruited 35% (n=10/29) in 4 months. Youth/families/clinicians requested the HELP pilot study be expanded to include youth seeking or receiving mental health support, adding new partners to our team (i.e., YouthNet/Réseau Ado, CHEO Youth Forum, 1Call1Click central intake). 26% (6/23) of teens enrolled in the next four months, with 5/6 youth having complete data. Most who expressed interest but did not enroll found the study questionnaires daunting as they were required to complete them virtually without researcher support. 83% (5/6) of enrolled youth demonstrated good engagement and measurable improvements in emotional health and lifestyle behaviours aligned with resource use. HELP resource engagement improved **
[figure not shown]
**sleep scores by 13%, decreased screen time by 0.96 hours/day and increased physical activity by 26 minutes/day. These changes allowed youth to achieve the recommended sleep and physical activity behaviours and reduce excessive screen use by approximately 50%.

Legend: Positive change was lower score for Strengths and Difficulties Questionnaire.

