**Rationale for Lifestyle Change interventions**

Youth are immersed in social media and doing little physical activity – poor lifestyle choices that impact their physical and mental health. Reviewing 102 health records of youth (50♀) receiving specialist support at CHEO we found few met criteria for major psychiatric diagnoses. Nevertheless, during the first two visits over 90% were counselled about changing sleep, physical activity and/or screen time. That mental health specialists are addressing the need for lifestyle change in the first visits with virtually all adolescents is evidence of the importance of lifestyle behaviour assessment/change as part of mental health treatment. There is a need to study lifestyle change intervention effectiveness in youth with mental illness because such interventions offer affordable, enjoyable, rewarding, and stigma-free treatment options that have no/few side effects/complications, and can be done individually or with family^14^. Healthy behaviours and moods spread through social networks, providing an opportunity for multiplier effects of lifestyle change on other family members, friends and neighbours^23^.

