### HELP E-Intervention

All study participants will have access to the HELP e-intervention either immediately (HELP access between 0 and 6 months) or after a wait of 6 months (control condition, access between 6 and 12 months). The use of a wait list control is expected to decrease the impact of randomization on study recruitment and retention. Our unique HELP e-resources utilize age-appropriate graphics and interactive formats developed collaboratively with youth/parent/clinician partners. There are 4 sections: 1) Know Your Habits, 2) Physical Activity, 3) Screen Time, 4) Sleep. Know Your Habits provides youth with their personal baseline questionnaire results. Messages are tailored to each youth’s readiness for behaviour change and assessment results. Each behaviour section (physical activity, screen time, sleep) has 4 sub-sections. “Learn” conveys information linking the behaviour and youth mental health and targets youth not yet contemplating behaviour change. “Pros and Cons” targets ambivalence, supporting youth to consider the barriers/facilitators of behaviour change. “Goals” guides youth to choose from >70 step-by-step change plans. Each plan contains a sequence of 6-8 steps that youth complete to achieve their goal. Steps vary in required time (2-30 mins) and youth proceed through the steps at their preferred pace. SMART goal, overcoming road blocks and additional kinesiologist support resources are also provided. Youth can track their goals and accomplishments on the website. Access to all HELP e-modules is available to all youth but the website suggests individualized avenues for change based on each participant’s assessment results. Sample pages from the HELP e-intervention are provided in Appendix H.

Each participant will have a unique login to the HELP e-intervention (found at www.cheoactive.ca). By automatically tracking e-resource use (site visits, interactivity use, knowledge component completion), the website provides data regarding participant engagement with the intervention. These data also assess the frequency or type of e-resource use, important considerations in analyzing the intervention impact on behaviour change. Comparing initial and post-intervention questionnaire responses will indicate the potential emotional health/lifestyle behaviour change impacts of HELP e-resource access.

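### The chart review for research question 5 does not, as described, separate HELP-prompted mentions from support the professional gives, so the recorded frequency may be inflated while a youth has HELP access

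*Protocol*

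**What the plan says.** Research Questions, question 5, asks whether mental health professionals supporting youth who engage with HELP "provide lifestyle behaviour support less frequently than for youth who do not receive the intervention". The target is therefore something professionals do.

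Study Assessments sets the extraction rule. Notes from all mental healthcare visits are read to "identify all content related to sleep, physical activity or screen time assessments, discussions or recommendations for change". The full text of each such note is kept after patient-specific information is removed. Chart review covers 18 months from enrolment and is done after the participant's 12-month assessment.

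Healthcare System Outcomes sets the coding. Each comment is "coded to indicate the focus (assessment, discussion, recommendation), content and information conveyed by the comment". The coding scheme is not new to this trial, since the work is to be done "utilizing the same procedures and coding framework developed during our retrospective chart review". The coded data are summarised descriptively and presented as how often lifestyle support occurs in mental health services. An inductive qualitative analysis by two team members is added.

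Summary of Work to Date gives the order of events. It begins with "Our review of the medical records for 102 youth receiving specialist mental health support at CHEO" and then says that the HELP "resources were then iteratively and collaboratively designed".

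HELP E-Intervention shows the overlap in topic: "There are 4 sections: 1) Know Your Habits, 2) Physical Activity, 3) Screen Time, 4) Sleep".

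**The concern.** The extraction rule is wider than the question. It takes in discussions as well as assessments and recommendations, and it does not ask who raised the topic. HELP works on the same three behaviours that the chart review looks for. A youth with access sets and tracks goals on them and has regular coordinator contact about them, so has a particular reason to mention them at a visit. A note recording only that a youth is working on a HELP sleep goal fits the extraction rule as a discussion, although the professional may have given no support.

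A framework developed before HELP had no such notes to classify, and the three attributes named in the protocol do not include HELP origin or who raised the topic. If these comments enter the tabulated frequency of lifestyle support, HELP can lower what professionals themselves provide while the recorded frequency falls less, or not at all. At stake is the answer to a secondary question, not the primary outcome.

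**Working it through.** The protocol states no expected frequency, effect or power for question 5, so there is no figure to reproduce. The check sets the passages side by side and then shows the mechanism with assumed numbers.

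**Passages**

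| Step | Place in protocol | Content |
| --- | --- | --- |
| Target | Research Questions, 5 | Support that professionals provide |
| Extraction | Study Assessments | All content on the three behaviours, discussions included |
| Coding | Healthcare System Outcomes | Focus, content, information conveyed; framework reused |
| Age of framework | Summary of Work to Date | 102-record review first, HELP afterwards (taken to be the review whose framework is reused; no other is described) |
| Access | Expected Duration of Participation | Intervention arm months 0-6; wait-list arm months 6-12 |

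No step between extraction and tabulation is said to set HELP-prompted mentions apart.

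**Illustration**

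The control level is taken from the protocol's own background. Rationale for Lifestyle Change interventions says that "during the first two visits over 90% were counselled about changing sleep, physical activity and/or screen time", and Summary of Work to Date gives 95% for lifestyle counselling within treatment. The following are assumptions with no source in the documents:
- a true reduction of 20 points under HELP access;
- m, the share of HELP youth without professional support whose notes still hold a HELP-prompted mention.

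Recorded proportion = p + (1 - p) x m, where p is the true proportion supported.

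| m | Control 90%, p = 70%: recorded | Difference | Control 95%, p = 75%: recorded | Difference |
| --- | --- | --- | --- | --- |
| 0 | 70% | 20 | 75% | 20 |
| 0.10 | 73% | 17 | 77.5% | 17.5 |
| 0.25 | 77.5% | 12.5 | 81.25% | 13.75 |
| 0.50 | 85% | 5 | 87.5% | 7.5 |

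The recorded difference is zero at m = 0.20/0.30 = 0.67 in the first case and at m = 0.20/0.25 = 0.80 in the second.

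This version counts youth with any mention. Question 5 asks how frequently support is given, so a count per youth or per visit may be closer to it. For a count, recorded mean = true mean + mean number of HELP-only mentions, and the reduction disappears when the second term equals it. No power is given, because no test is specified for these coded frequencies.

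**Check on a tempting remedy**

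Suppose the main frequency left out every comment that refers to HELP. Assume no true effect, 90% supported in both arms, and 30% of supported HELP youth whose only counselling refers to HELP. The HELP arm is then recorded at 0.90 x 0.70 = 63%, a spurious reduction of 27 points. Blanket exclusion replaces a bias against the hypothesis with one in its favour.

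**The case against.** The strongest reply is that an extraction rule is not a counting rule. The focus code already separates assessments and recommendations, which are professional acts, from discussions. The framework is in an unpublished manuscript, and the extraction form is in an appendix that is not shown. The content and information codes might capture a HELP reference. Full text is kept, so comments can be recoded, and the inductive analysis may bring HELP-related talk to light.

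Much of this stands, and it limits the claim. It cannot be said that the framework has no usable code, only that none is described. The exposure lies mainly in the discussion category. What does not stand is that the safeguards settle the matter: none of them is said to separate HELP mentions from the frequency, and attribution rules are better fixed before extraction than devised afterwards.

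Two stronger readings are tempting. A reader might infer that the artefact falls on one arm only. It does not: wait-list youth receive HELP in months 6-12, so it follows access period, and both arms have six months of access within the 18-month window. Control youth also complete questionnaires on the same behaviours, so study-related mentions are not confined to HELP users. A reader might also infer that a note naming HELP reveals the arm to the coder. Since both arms receive HELP, it does so only together with its timing, and the protocol does not say that the coders are blinded.

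**Conclusion.** The concern holds as a possibility that the plan leaves open. Extraction takes all content on the three behaviours, coding reuses a framework older than HELP, and nothing described separates a youth's HELP-prompted mention from professional support. During HELP access this could inflate the recorded frequency and mask the reduction that question 5 looks for.

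The size is unknown. The illustrated shrinkage, from 20 points to between 5 and 17.5 for m between 0.10 and 0.50, rests on an assumed true reduction and assumed mention rates. The 90% and 95% anchors come from youth already in specialist care, whereas the trial also enrols youth who are seeking or waiting for support. A reader might conclude that the answer to question 5 will be wrong or reversed. The documents do not support that: they give no mention rate, the summary is descriptive, and the retained text allows recoding.

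**What to change.** Before extraction starts, add two fields to the extraction form and coding frame, applied identically in both arms and all periods:

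- the comment refers to HELP or the study (yes/no);
- the topic was raised by the professional, by the youth or family, or unclear.

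For question 5, tabulate professional assessment, counselling or recommendation separately from youth-reported mentions with no professional action. Counselling that builds on HELP goals stays in the professional category. Report the all-content count and the count without HELP-referring comments as sensitivity results, each by access period.

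Do not define the main frequency by excluding every HELP reference, for the reason shown in the working. Do not redact HELP from the text used for the inductive analysis, which should be able to describe it.

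The cost is two fields, slightly more coding time and some entries coded unclear. Because extraction follows the 12-month assessment, the change can be made before it begins.
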